### Data acquisition

All patient data will be collected during the initial visit and routine follow-up visits (occurring around month 1, quarterly and at final assessment) or by mail, telephone or email (Table 3). Demographic data and clinical characteristics will be collected from medical records if available, or by patient interviews. Patient-reported treatment satisfaction will be assessed using a specific treatment satisfaction questionnaire: the validated Anti-Clot Treatment Scale (ACTS), as used in the EINSTEIN DVT and EINSTEIN PE studies [24,25].

**Table 3 T3:** Overview of data collection procedures

**Scheduled procedure**	**Initial visit (baseline)**	**After 1 month**	**Quarterly**	**Final assessment**
Visit date	X	X	X	X
Demographic data	X			
Medical/surgical history	X			
Concomitant diseases	X		X*	X*
Concomitant medication/treatment	X		X*	X*
Physical examination	X			
Laboratory results (if available)	X	X	X	X
Diagnosis of current DVT	X			
Previous VTE	X			
Current VTE treatment regimen	X		X	X
Initial phase treatment		X		
Dose reduction (twice daily to once daily)		X		
Assessment of therapy				X
Patient satisfaction and adherence with treatment (optional, only in a sub-sample of patients)		X*	X*	X*
Adverse events^†^		X	X	X

*Only documented if new information is available from regular practice. No additional diagnostics are required for the study; ^†^serious adverse events must be reported to the sponsor within 24 hours.

DVT, deep vein thrombosis; VTE, venous thromboembolism.

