XALIA is being conducted in response to a request made by the European Medicines Agency (EMA) to evaluate rivaroxaban for the treatment of acute DVT after the completion of the large phase III EINSTEIN DVT study. The EINSTEIN phase III clinical programme investigated the use of rivaroxaban as a single-drug approach in contrast to the current dual-drug paradigm of enoxaparin/VKAs [8,9]. EINSTEIN DVT was a randomized, open-label, event-driven, non-inferiority trial that investigated the efficacy and safety of oral rivaroxaban (15 mg twice daily for 21 days followed by 20 mg once daily) compared with subcutaneous enoxaparin (1 mg/kg body weight twice daily for at least 5 days) overlapping with and followed by a VKA (warfarin or acenocoumarol, started within 48 hours after randomization), in patients with acute, symptomatic, objectively confirmed proximal DVT without PE. Treatment duration was at the discretion of the attending physician and was planned for 3, 6 or 12 months [8]. In EINSTEIN DVT, rivaroxaban was shown to be non-inferior to enoxaparin/VKA for the reduction of recurrent VTE (Table 1) [8]. Rates of first major or non-major clinically relevant bleeding (the primary safety outcome) were similar in patients receiving rivaroxaban compared with patients receiving enoxaparin/VKA. In addition, rivaroxaban was associated with a significantly improved net clinical benefit (defined as the composite of symptomatic, recurrent VTE and major bleeding), compared with enoxaparin/VKA (Table 1) [8]. The consideration of patient-reported outcomes is becoming increasingly important when evaluating the overall effectiveness of direct oral anticoagulants. It is worth noting that an EINSTEIN DVT subanalysis showed that rivaroxaban was associated with improved treatment satisfaction compared with enoxaparin/VKA therapy in patients with DVT [24]. Among the factors noted were a reduction in patient-reported anticoagulation burden and an increase in convenience [24]. It would, therefore, be desirable to confirm the influence of rivaroxaban treatment on patient lives in routine care.

**Table 1 T1:** Efficacy and safety outcomes of the phase III EINSTEIN DVT study

	**Rivaroxaban**	**Enoxaparin/VKA**	**HR (95% ****CI)**	**P value**
**Efficacy outcomes (ITT population)**	(n = 1731)	(n = 1718)		
Recurrent VTE* (%)	2.1	3.0	0.68 (0.44–1.04)	<0.001
**Safety outcomes (safety population)**	(n = 1718)	(n = 1711)		

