### Study outcomes

Primary study outcomes are the incidence of treatment-emergent adverse events, namely major bleeding, symptomatic recurrent venous thromboembolic events and all-cause mortality. Major bleeding is defined as overt bleeding associated with a fall in haemoglobin of ≥2 g/dl; or a transfusion of ≥2 units of packed red blood cells or whole blood; or bleeding at a critical site (intracranial, intraspinal, intraocular, pericardial, intra-articular, intramuscular with compartment syndrome, retroperitoneal); or death. Secondary outcomes include: major cardiovascular events; patient-reported treatment satisfaction and adherence; healthcare resource utilization; reasons for drug switching or interruption of treatment; and adverse events, including serious adverse events. Data on patients with renal impairment treated for acute DVT within the terms of the local product information will also be collected and analysed. The Adjudication Committee, blinded to the treatment group, will adjudicate bleeding events; recurrent VTE and other thromboembolic events; major cardiovascular events; and cause of death. Local objective diagnosis of symptomatic recurrent venous thromboembolic events is a prespecified criterion for event adjudication.

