### Statistical analysis

The primary statistical analysis includes a descriptive analysis of the primary and secondary outcomes. The primary outcome variable is the incidence of treatment-emergent adverse events, namely major bleeding and symptomatic recurrent VTE. An adverse event is considered as treatment emergent if it starts on or after the day of the first dose of study medication and ≤2 days after the last dose. All patients who took at least one dose of medication will be included in the safety population. For primary and secondary variables, incidence proportions and incidence rates will be estimated, together with 95% confidence intervals. The accepted range for the 95% confidence intervals is estimated to be between the allocation ratios of 1:3 and 3:1; therefore, at least 25% of patients at each study centre should receive either standard of care or rivaroxaban therapy. To compare the treatment arms, the risk difference and corresponding 95% confidence interval will be calculated, and time-to-event analyses will be conducted.

The potential for allocation bias in open-label, non-randomized studies will be minimized by also presenting a propensity score analysis to control the effect of unbalanced covariates [26,27]. To minimize selection bias, physicians will be asked to document patients consecutively. To decrease the possibility of reporting bias, source data will be verified at approximately 10% of study centres in countries where this is legally possible. A sample size of 4800 patients assumes that 17% of patients will be non-evaluable because of non-overlapping propensity scores or because of withdrawn informed consent forms.

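### Table 3 makes the recording of treatment satisfaction and adherence conditional on new information from regular practice, a rule that does not suit a study questionnaire

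*Protocol article*

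**What the plan says.** The Study outcomes section lists, among the secondary outcomes, "patient-reported treatment satisfaction and adherence; healthcare resource utilization", with no restriction to part of the cohort. The Data acquisition section says: "Patient-reported treatment satisfaction will be assessed using a specific treatment satisfaction questionnaire", and names ACTS as the instrument.

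Table 3, in the same section, gives the row as "Patient satisfaction and adherence with treatment (optional, only in a sub-sample of patients"). It has no entry at the initial visit. The entries at month 1, quarterly and final assessment each carry an asterisk, explained as: "Only documented if new information is available from regular practice". The note adds that the study requires no extra diagnostics.

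The Statistical analysis section states: "The primary statistical analysis includes a descriptive analysis of the primary and secondary outcomes". It continues: "To compare the treatment arms, the risk difference and corresponding 95% confidence interval will be calculated", together with time-to-event analyses. On selection it says: "To minimize selection bias, physicians will be asked to document patients consecutively". A propensity score analysis is to address unbalanced covariates.

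**The concern.** The running text and the table give sites different instructions. The text says satisfaction will be measured with a questionnaire. The table says the item is documented only when routine care yields something new. Routine care does not produce an ACTS score; someone has to hand the patient the form for the study's purposes. A site that follows the table literally could leave the row blank at every contact, or complete it only when something has changed or been mentioned.

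Recording could then depend on the patient's experience of treatment. The measure is subjective, and physician and patient both know the drug. If the dependence differs between the rivaroxaban and standard-therapy cohorts, the two descriptions of satisfaction and adherence differ for reasons unrelated to treatment. The Rivaroxaban section gives this outcome some weight, referring to the phase III satisfaction result: "It would, therefore, be desirable to confirm the influence of rivaroxaban treatment on patient lives in routine care".

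**Working it through.** The documents give no ACTS sample size, response rate, SD or expected difference, so there is no figure to reproduce. The check is a reading of Table 3, followed by an illustration.

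**1. The starred rows compared**

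| Row | Initial visit | Month 1 | Quarterly | Final |
|---|---|---|---|---|
| Concomitant diseases | X | – | X* | X* |
| Concomitant medication/treatment | X | – | X* | X* |
| Satisfaction and adherence | – | X* | X* | X* |

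The first two rows have an unstarred baseline entry, so new information means a change from a recorded starting point. The third has no baseline and no unstarred cell. At month 1 there is no earlier reading for anything to be new against, and at no contact does the table require the questionnaire. The row label already says that the item is optional and in a sub-sample, so the asterisk is not needed to convey that. Where the table means only that an item depends on availability (laboratory results), it says so in the row label and uses no asterisk.

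**2. Do the stated safeguards reach this point?** Consecutive documentation governs entry to the study. The propensity score addresses treatment allocation. The 17% non-evaluable allowance covers non-overlapping scores and withdrawn consent. Blinded adjudication covers clinical events. None is stated to cover whether a questionnaire is completed.

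**3. Simple illustration (all inputs assumed).** Let a share r of a cohort respond, and let non-responders score 0.5 SD lower than responders. The responder mean then exceeds the cohort mean by (1 − r) × 0.5 SD.

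- r = 0.60: 0.40 × 0.5 = 0.20 SD
- r = 0.40: 0.60 × 0.5 = 0.30 SD
- r = 0.20: 0.80 × 0.5 = 0.40 SD

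With no true difference, 40% against 60% gives 0.30 − 0.20 = 0.10 SD, and 20% against 60% gives 0.40 − 0.20 = 0.20 SD. Equal r with the same gap gives 0.

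**4. Comparison with sampling error (second model, also assumed).** Evaluable patients: 4800 × (1 − 0.17) = 3984, or 1992 per cohort if equal. Let a share f have a recorded score in each cohort. Response follows a probit model with correlation ρ between satisfaction and response, and the score SD is 1. The responder mean is ρ × φ(c)/f with c = Φ⁻¹(f). The false difference is therefore (ρ₁ − ρ₀) × φ(c)/f, and the 95% half-width is 1.96 × √(2/(1992 f)). With ρ₁ = 0.2 and ρ₀ = 0:

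| f | Recorded per cohort | False difference (SD) | 95% half-width (SD) |
|---|---|---|---|
| 10% | 199 | 0.351 | 0.196 |
| 25% | 498 | 0.254 | 0.124 |
| 50% | 996 | 0.160 | 0.088 |
| 75% | 1494 | 0.085 | 0.072 |

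With ρ₁ = ρ₀ = 0.1 the false difference is 0 at every f. With 0.2 against 0.1 it is 0.175, 0.127, 0.080 and 0.042 SD, close to or below the half-width. Selective recording can exceed sampling error, but only when it differs enough between cohorts. The half-widths treat every evaluable patient as eligible for the questionnaire; a smaller sub-sample would widen them.

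**The case against.** The strongest reply is that this is an overview table in a condensed article about a non-interventional study. The asterisk may express only that design, as the remark on extra diagnostics suggests, and sites may have understood it as recording a questionnaire whenever one exists. That reading is possible, but it is not what the footnote says, and the conflict with the ACTS sentence remains in print.

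A reader might infer more than the article supports:

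- **That respondents are proven to be self-selected.** The word optional does not say whether the choice lies with the patient, the centre or the country.
- **That the sub-sample is chosen after treatment starts.** The absence of a baseline entry shows only when satisfaction is measured, and satisfaction with a treatment cannot be measured before it is experienced.
- **That a selection rule for the sub-sample is missing.** An article commonly leaves that to the full protocol.
- **That a study aim is unmet.** The article calls confirmation of the satisfaction finding desirable; its main objective is safety.

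Two further objections stand. No comparison of ACTS scores between cohorts is specified; the risk difference and time-to-event methods are stated in general terms and do not describe a scale score. And the illustrated bias rests wholly on assumptions and could partly persist after the fix, because offering a questionnaire to everyone does not make everyone answer.

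**Conclusion.** The point holds as a fault in a stated collection rule. Table 3, followed as written, makes recording of a named secondary outcome conditional on something that routine care does not supply, and it conflicts with the statement that ACTS will be used. Satisfaction and adherence described by cohort can be biased if recording differs between cohorts.

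The size cannot be determined from the article. The illustrations give 0.10 to 0.20 SD under the simple model, 0.042 to 0.351 SD under the unequal-correlation scenarios shown, and zero when selection is equal. They show that the problem could matter, not that it occurred. The primary outcomes of major bleeding, recurrent VTE and all-cause mortality are unaffected. This is a worthwhile, inexpensive improvement to one secondary outcome.

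**What to change.** Remove the asterisk from the satisfaction and adherence row of Table 3 and from the matching site instructions. Within the optional sub-sample, however the full protocol defines it, offer ACTS and the adherence items to every patient in both cohorts at month 1, each quarterly contact and final assessment, whether or not there is new information. Report completion by cohort and visit, compare baseline characteristics of responders and non-responders, and describe any cohort difference as limited to responders.

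The cost is some extra questionnaires. The contacts are already scheduled, and the article allows data collection by mail, telephone or email. Timing matters: enrolment began in June 2012 and recruitment was due to finish in early 2014. Under a mid-study change, contacts already past cannot be recovered, and data collected before and after the change should be flagged and shown separately. If the asterisk is only a printing slip, correcting the table and reporting completion is enough.

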### Statistical analysis

The primary statistical analysis includes a descriptive analysis of the primary and secondary outcomes. The primary outcome variable is the incidence of treatment-emergent adverse events, namely major bleeding and symptomatic recurrent VTE. An adverse event is considered as treatment emergent if it starts on or after the day of the first dose of study medication and ≤2 days after the last dose. All patients who took at least one dose of medication will be included in the safety population. For primary and secondary variables, incidence proportions and incidence rates will be estimated, together with 95% confidence intervals. The accepted range for the 95% confidence intervals is estimated to be between the allocation ratios of 1:3 and 3:1; therefore, at least 25% of patients at each study centre should receive either standard of care or rivaroxaban therapy. To compare the treatment arms, the risk difference and corresponding 95% confidence interval will be calculated, and time-to-event analyses will be conducted.

The potential for allocation bias in open-label, non-randomized studies will be minimized by also presenting a propensity score analysis to control the effect of unbalanced covariates [26,27]. To minimize selection bias, physicians will be asked to document patients consecutively. To decrease the possibility of reporting bias, source data will be verified at approximately 10% of study centres in countries where this is legally possible. A sample size of 4800 patients assumes that 17% of patients will be non-evaluable because of non-overlapping propensity scores or because of withdrawn informed consent forms.

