**(composite of symptomatic, recurrent VTE plus major bleeding, %)**				

*Primary efficacy outcome; ^†^principal safety outcome.

CI, confidence interval; DVT, deep vein thrombosis; HR, hazard ratio; ITT, intention to treat; PE, pulmonary embolism; VKA, vitamin K antagonist; VTE, venous thromboembolism.

The EINSTEIN PE study investigated rivaroxaban in patients with acute, symptomatic PE, and also showed that it was non-inferior to enoxaparin/VKA, with a 51% reduction in the incidence of major bleeding [9]. The EINSTEIN EXT study investigated rivaroxaban in patients receiving long-term treatment in whom there was no clear decision about continuing or stopping anticoagulation; rivaroxaban was superior to placebo in the reduction of recurrent VTE, and showed an acceptable benefit–risk balance [8].

Rivaroxaban is the first direct oral anticoagulant to be approved for the treatment of DVT and PE and secondary prevention of VTE in the European Union, US and Canada. XALIA is a multicentre, prospective, non-interventional, observational study taking place across more than 20 European countries, and other countries including Israel and Canada. XALIA will assess whether the results obtained with rivaroxaban in real-world clinical practice in patients with objectively confirmed, acute DVT and an indication to receive anticoagulation for at least 3 months are consistent with those seen in the phase III EINSTEIN DVT study.

The main objective of the study is to evaluate the safety of rivaroxaban in routine clinical practice for the treatment of acute symptomatic DVT and prevention of recurrent VTE by examining the incidence of treatment-emergent adverse events: major bleeding, symptomatic recurrent venous thromboembolic events and all-cause mortality.

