### Centre and patient selection

Recruitment of patients will be conducted by investigators at selected study centres in Europe and other regions in which rivaroxaban is approved. Enrolment is planned for approximately 4800 patients with approximately equal numbers in each arm. Patients can be enrolled immediately after a decision about the choice of anticoagulant therapy has been made, but no randomization will be undertaken. Inclusion and exclusion criteria are summarized in Table 2.

**Table 2 T2:** Inclusion and exclusion criteria for XALIA

**Inclusion**	**Exclusion**
● Female or male patients who are ≥18 years of age	● Patients with acute symptomatic PE*
● Diagnosis of acute DVT, objectively confirmed	● Other exclusion criteria are dependent on local product information
● Indication for anticoagulation therapy for at least 12 weeks	
● Patients willing to participate in the study and available for follow-up	

*A parallel symptomatic PE is not an exclusion criterion; however, XALIA will not enrol patients with only PE.

DVT, deep vein thrombosis; PE, pulmonary embolism.

Patients who are ≥18 years old, with a diagnosis of objectively confirmed, acute DVT and an indication to receive anticoagulation for ≥3 months will be included. If anticoagulation is administered for a shorter period than planned, patients will remain in the study.

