## Discussion

The demand for real-world data in addition to clinical trial data is increasing. Non-interventional studies are crucial for obtaining a different perspective on the safety and effectiveness of drugs when used in routine clinical practice. Unlike registry data, which is typically analysed retrospectively, studies such as XALIA are designed to assess prospectively defined outcomes of interest thus eliminating potential bias. It is anticipated that XALIA will provide important information on the treatment of DVT in a heterogeneous patient population in a real-world setting. Strict inclusion and exclusion criteria in randomized clinical trials, such as EINSTEIN DVT, may restrict the population in which therapies can be studied, and it is important to show that the findings from clinical trials are applicable to patients treated in routine clinical practice.

One challenge with open-label observational studies is the potential for increased reporting of adverse events with the new drug, otherwise known as the Weber effect [28]. This may be a result of increased patient exposure and higher interest in the drug; however, when physicians become familiar with the drug and its adverse event profile, the rate of reported adverse events usually declines [28]. Therefore, it may be anticipated that this effect will also occur with rivaroxaban, at least during the initial period after its approval for the treatment of VTE.

Findings from XALIA may enable healthcare professionals to gain new insights into the management of patients with DVT, particularly regarding the risks of bleeding and recurrent VTE. Patients are at an immediate and continued risk of recurrence after the first venous thromboembolic event [29], and this risk can be substantial after cessation of anticoagulation [30,31]. Real-world data on recurrence rates will, therefore, be meaningful, particularly in patients who may discontinue anticoagulation. In some cases, the optimal duration of anticoagulation therapy for DVT is unclear; this may be partly owing to challenges in maintaining an appropriate benefit–risk balance because of an increased risk of bleeding or a patient’s intrinsic risk factors [5]. It is hoped that by evaluating the incidence and type of thromboembolic events and bleeding events in XALIA, an accurate representation of the benefit–risk profile of rivaroxaban in routine care will be provided.

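### Recurrent VTE, and on some wording death, are primary events only up to 2 days after the last dose; a prespecified full-follow-up analysis and one consistent definition are needed

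*Protocol article*

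**What the plan says.** The main objective, at the end of the Rivaroxaban subsection, is to examine the "incidence of treatment-emergent adverse events: major bleeding, symptomatic recurrent venous thromboembolic events and all-cause mortality". The Study outcomes section repeats this: "Primary study outcomes are the incidence of treatment-emergent adverse events, namely major bleeding, symptomatic recurrent venous thromboembolic events and all-cause mortality". The Statistical analysis section gives a shorter list: "The primary outcome variable is the incidence of treatment-emergent adverse events, namely major bleeding and symptomatic recurrent VTE". It then defines an adverse event as treatment-emergent if it "starts on or after the day of the first dose of study medication and ≤2 days after the last dose".

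Follow-up does not end with treatment. Under Centre and patient selection: "If anticoagulation is administered for a shorter period than planned, patients will remain in the study". The opening of XALIA study design runs the study to 12 months after the last enrolment and leaves treatment duration to the attending physician alone. The Drug administration section has switching and cessation documented, and Table 3 schedules adverse-event collection at month 1, quarterly and at final assessment. The Discussion says: "Real-world data on recurrence rates will, therefore, be meaningful, particularly in patients who may discontinue anticoagulation".

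For estimation, the Statistical analysis section plans incidence proportions and incidence rates with 95% confidence intervals, risk differences between arms, time-to-event analyses, and a propensity score analysis for unbalanced covariates.

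**The concern.** A short on-treatment window is a usual convention for bleeding, where the question is what happens under exposure. Recurrence and death are different, because the reason for stopping may carry information about the risk of the event. If treatment is withdrawn in a patient who is deteriorating, a death a week later falls outside the count. If one arm has more such withdrawals, or stops earlier, its on-treatment figures change for reasons unrelated to the drug.

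Allocation is not randomised, and the end of the window is a clinical decision made after baseline, so the arms may well differ in when and why treatment stops. Two things are at stake: the validity of the between-arm comparison of VTE and death, and whether the headline recurrence figure includes events in the patients whom the Discussion singles out. Separately, the article does not say consistently whether mortality is subject to the window at all.

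**Working it through.** **1. The definitions side by side**

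| Place | Major bleeding | Recurrent VTE | All-cause mortality |
|---|---|---|---|
| Abstract | treatment-emergent | can be read as outside the label | can be read as outside the label |
| Main objective | treatment-emergent | treatment-emergent | treatment-emergent |
| Study outcomes | treatment-emergent | treatment-emergent | treatment-emergent |
| Statistical analysis | treatment-emergent | treatment-emergent | not listed |

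For recurrent VTE the Statistical analysis section alone settles the matter: onset on day 3 after the last dose is not a primary event. For mortality the conclusion needs the main objective or Study outcomes read with the 2-day definition. The definition also refers to when an adverse event starts, so it is unclear whether a later death from an event that began on treatment counts.

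**2. What the planned methods do and do not handle**

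Take an assumed on-treatment hazard of 2% per year in both arms, with 4 months of treatment in one and 8 in the other. The proportions are about 2% × 4/12 = 0.67% and 2% × 8/12 = 1.33%, a difference due only to window length. The incidence rate is 2% per year in both, so rates and time-to-event analyses deal with unequal duration. They do so only if stopping is unrelated to the patient's risk. A propensity score for treatment allocation balances baseline covariates and cannot correct for what leads to stopping later.

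**3. Recurrences outside the window (illustration)**

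The article gives no figure to reproduce here. Inputs from the article: 4800 patients, 17% non-evaluable and roughly equal arms, so 4800 × 0.83 = 3984, or 1992 per arm. Inputs assumed: 30–70% stop during follow-up, 3–9 months are observed off treatment, and off-treatment recurrence is 3–10% per year.

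Events after stopping = 1992 × share stopping × (1 − exp(−hazard × time)). Those counted use 2/365.25 years as the time.

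| Share stopping | Time off treatment | Hazard per year | Events per arm | Counted in 2 days | Not counted |
|---|---|---|---|---|---|
| 30% | 3 months | 3% | 4.5 | 0.10 | 4.4 |
| 50% | 6 months | 5% | 24.6 | 0.27 | 24.3 |
| 70% | 9 months | 10% | 100.8 | 0.76 | 100.0 |

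For scale, Table 1 recurrence of 2.1% and 3.0% gives 1992 × 0.021 = 42 and 1992 × 0.030 = 60 events per arm. Using these as a stand-in for the on-treatment count is a further assumption. In the middle row the uncounted share is 24.3/(24.6 + 59.8) = 29% to 24.3/(24.6 + 41.8) = 37%. Across the three rows it runs from 4.4/(4.5 + 59.8) = 7% to 100.0/(100.8 + 41.8) = 70%.

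**4. Mortality (illustration)**

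Start from Table 1: 2.2% v 2.9%, ratio 2.2/2.9 = 0.76. Multiply each risk by (1 − assumed share of deaths more than 2 days after the last dose).

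| Missed, rivaroxaban | Missed, standard | Counted risks | Ratio |
|---|---|---|---|
| 40% | 40% | 1.32% v 1.74% | 0.76 |
| 20% | 40% | 1.76% v 1.74% | 1.01 |
| 40% | 20% | 1.32% v 2.32% | 0.57 |

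Equal shares leave the ratio intact but understate both risks. Unequal shares move it either way.

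**The case against.** The strongest reply is that this is a safety study of a drug in use, for which an on-treatment estimate is legitimate. Physicians set duration, so an all-follow-up count mixes in off-drug time and stopping practice, and the arm that stops sooner may then look worse. That stands: replacing the on-treatment analysis is a debatable choice of estimand, not the correction of an error. It does not argue against reporting both.

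A second reply is that rates and time-to-event analyses are planned. They answer unequal treatment duration, as shown in the working, but not prognosis-related stopping.

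A third is that a condensed article may leave supplementary analyses to the full protocol or SAP. That is fair as to their absence. But the article itself fixes the primary definition, and its sections disagree on mortality.

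Three stronger readings are tempting and are not supported:

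- A reader might infer that the plan cannot address recurrence after discontinuation. Patients remain in the study, cessation is documented, adverse events are collected to final assessment, and adjudication of recurrent VTE and cause of death has no stated window. Later events are outside the primary count; nothing says that they are discarded. The sentence on discontinuation is also Discussion commentary, not an objective.
- A reader might infer a mismatch with EINSTEIN DVT from the Table 1 label "Efficacy outcomes (ITT population". That label says who was analysed. The article does not give that trial's event-counting window, and Table 1 lists mortality under the safety population.
- A reader might suppose that most recurrences are lost. With everyone treated for exactly 6 months and followed for 6 more, 2% per year on treatment and 5–8% off, the share is 5/7 = 71% to 8/10 = 80%. That pattern is assumed, and it lies above the range in the working.

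**Conclusion.** The point holds in limited form. For recurrent VTE, the primary count clearly excludes onset more than 2 days after the last dose. For all-cause mortality, the main objective and Study outcomes imply the same exclusion, while the Statistical analysis section and the Abstract leave it in doubt; that inconsistency needs correcting in its own right.

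The on-treatment comparison of these two outcomes can be biased in either direction if stopping relates to prognosis and differs by arm, and nothing among the methods the article describes removes this. That stopping is informative is an inference from its being the physician's decision; the article gives no data on it. The size cannot be derived from the document. The ranges of 4 to 100 uncounted recurrences per arm and of 0.57 to 1.01 for a mortality ratio of 0.76 rest on assumed stopping shares, off-treatment hazards and missed-death shares. The article also states no target precision against which to set them. The 2-day window for major bleeding is not in question.

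**What to change.** 1. State one definition of recurrent VTE and one of all-cause mortality, and use them in the Abstract, the main objective, Study outcomes and Statistical analysis. Say whether mortality is a primary outcome, and whether a death is placed by its date or by the start of the fatal event.
2. Keep the 2-day window for major bleeding.
3. Alongside the on-treatment analysis, prespecify an analysis of all adjudicated recurrent VTE and all deaths from start of treatment to end of follow-up, by initial treatment cohort and regardless of stopping or switching.
4. Report both versions side by side, with time on treatment and reasons for stopping by arm, so that a reader can judge how far stopping explains any gap between them.

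The cost is mainly wording and one further set of tables, because follow-up after stopping, the scheduled contacts and adjudication are already planned. The downside is that the full-follow-up estimate includes off-drug time and reflects stopping practice, which is why it accompanies the on-treatment result and does not replace it. The definitions should be settled before the data are analysed.
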